**Secondary subobjectives**
Assess the usability and acceptability of continuous accelerometry monitoring using patient feedback questionnairesAssess retrospectively the accuracy of Rheumatoid Arthritis Flare Questionnaire (RA-FQ) flare prediction vs clinically confirmed flareDevelop and evaluate a combined dynamic prediction model incorporating longitudinal accelerometry-derived measurements and the RA-FQ total score to predict clinically confirmed flare and compare its performance with that of the accelerometry-only model

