##### RA-FQ

The RA-FQ is also designed to remotely monitor patients with RA during drug tapering. Participants rate, on a 0‐10 scale, their pain, difficulty with physical activities, fatigue, joint stiffness, and challenges in daily activities such as work, over the past week. At the end of the questionnaire, 2 yes or no questions ask whether the patient has experienced these symptoms for more than 1 week and whether they believe they are currently experiencing a flare of RA. The responses provide a standardized way to assess symptom severity and detect flares, helping clinicians track disease activity and adjust treatment if needed. The questionnaire will be collected weekly for each patient. For the 0‐10 scale items, the average score for each symptom will be calculated across all patients at 4 main visit time points, and summary statistics (eg, mean, SD, and/or median, IQR, and range) will be reported.

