The model will be generated at weekly landmark times throughout follow-up. At each landmark, the model will use all accelerometry data collected up to that time to estimate the probability of clinician-defined flare occurring within the subsequent 14 days. Weekly updating allows risk estimates to be refreshed throughout DMARD tapering and provides clinically actionable information to support decisions regarding continuation or modification of tapering.

We will also evaluate the accuracy of the model’s flare predictions for each prediction time window against patient-reported flares derived from the RA-FQ, based on responses to the yes or no question about current flare status. Patient-reported flare status will serve as the reference standard. Model-predicted flares will be compared against patient reports to calculate sensitivity, specificity, and agreement (Cohen κ). It helps to assess how well the model’s predictions align with patient perception.

Sensitivity: proportion of patient-reported flares that are correctly predicted by the model (true-positive rate); higher values, close to 100%, are desirable.Specificity: proportion of patient-reported nonflares that are correctly identified as no flare by the model (true-negative rate); higher values, close to 100%, are desirable.Agreement: measured using Cohen κ to quantify concordance between model-predicted and patient-reported flares; higher values, close to 1, indicate stronger agreement beyond chance.

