### Secondary Analyses

Our secondary objectives are to assess the usability and acceptability of continuous accelerometry monitoring using patient feedback questionnaires, retrospectively assess the accuracy of RA-FQ flare prediction vs clinically confirmed flare, and develop and evaluate a combined dynamic prediction model to investigate whether incorporating RA-FQ total scores alongside accelerometry-derived measurements improves the prediction of clinically confirmed flare.

Participant acceptability of continuous accelerometry monitoring will be assessed using a structured feedback questionnaire (Axivity Feedback Survey). The survey evaluates usability, comfort, technical issues, and impact on daily life (Section A: categorical and ordinal items), as well as overall satisfaction (0‐100 scale) and free-text comments (Section B).

Quantitative responses will be summarized descriptively. Categorical and ordinal items will be reported as frequencies and percentages, with graphical presentation where appropriate. The overall satisfaction score will be summarized using mean, SD, median, IQR, and range. Comparisons between time points (where applicable) may be explored using nonparametric tests. The free-text responses in Section B will not be analyzed, as they would require a qualitative analysis.

We also plan to refit the landmarking models for arthritis flare, using accelerometry data as longitudinal predictors and patient-reported flares from the RA-FQ as the outcome. This approach will help identify potential associations between accelerometry measures and patient-reported flares. Then, model-predicted flares will be compared against clinically confirmed flares to calculate sensitivity, specificity, and agreement (Cohen κ). This approach also allows us to assess how well the model’s predictions align with clinically confirmed flares.

Comparing the performance of these models with the ones mentioned in primary analyses will help assess whether accelerometry-derived signals are consistently predictive across different definitions of flare. If both models perform well, this will strengthen confidence that the signals are robust and not dependent on a single definition of flare.

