As another secondary analysis, we will develop a combined dynamic prediction model to investigate whether incorporating patient-reported symptom information alongside accelerometry-derived measurements improves the prediction of clinically confirmed flare. The model will incorporate both longitudinal accelerometry-derived measures and the RA-FQ total score available at or before each prespecified landmark time. The RA-FQ captures patients’ subjective experiences of symptoms, including pain, stiffness, fatigue, and function, whereas accelerometry provides device-derived quality metrics and physical activity measures. The performance of the combined model will be compared with that of the accelerometry-only model using measures of discrimination and calibration to evaluate the additional predictive value of the RA-FQ.

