### Strength and Limitations

The main strength of this study is its embedding within an existing NHS DMARD tapering service, which improves real-world relevance and feasibility. Study visits are aligned with routine ROADMAP clinic appointments to reduce patient burden, and ad hoc flare visits are incorporated to capture clinically meaningful events when they occur. The protocol also includes practical accommodations for patients who cannot use the REDCap portal by offering paper RA-FQs, which may improve inclusivity and reduce avoidable exclusion related to digital access. Another strength is the multimodal design, combining clinician assessment, PROMs, and continuous wearable data. This supports richer phenotyping of flare-related change and may improve prediction performance compared with relying on any single data stream alone. The planned diagnostic evaluation using AUC, sensitivity, specificity, and predictive values is also appropriate for assessing clinical utility in an early development phase.

The protocol also has limitations. It is a single-site observational study, so external validity may be limited, and the findings may reflect local service pathways, patient selection, and tapering practices. The target sample is intended to support model development and pilot evidence rather than definitive effectiveness conclusions. In addition, flare classification depends partly on clinical review timing, which may introduce timing uncertainty in the reference outcome. The protocol acknowledges this and includes procedures for delayed final classification and investigator clinical discretion when the DAS28-CRP is elevated for reasons unrelated to inflammatory arthritis.

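### The combined model is compared only with accelerometry alone, so the plan does not estimate what the wearable adds to the weekly RA-FQ

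*Protocol article*

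**What the plan says.** The combined model takes accelerometry measures and the RA-FQ total score as longitudinal inputs and predicts clinically confirmed flare. Secondary Analyses names one comparator: "The performance of the combined model will be compared with that of the accelerometry-only model using measures of discrimination and calibration", and gives the purpose as "to evaluate the additional predictive value of the RA-FQ". The secondary subobjectives in Textbox 1 name the same comparator ("compare its performance with that of the accelerometry-only model"), and the fifth aim in the Abstract runs in the same direction.

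The RA-FQ appears in three other places:

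- In Primary Analyses it is the yardstick for the accelerometry model: "Patient-reported flare status will serve as the reference standard".
- Secondary Analyses lists an objective to "retrospectively assess the accuracy of RA-FQ flare prediction vs clinically confirmed flare".
- The analysis then described in that section refits the landmark models "using accelerometry data as longitudinal predictors and patient-reported flares from the RA-FQ as the outcome", and scores those predictions against clinical flare.

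Strength and Limitations says that the multimodal design "may improve prediction performance compared with relying on any single data stream alone".

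**The concern.** Two data streams give a combined model two single-stream comparators, and the plan uses one. The Introduction describes the RA-FQ as an established instrument that patients complete remotely, without attending hospital. The wearable asks for more: continuous wear, with three devices in sequence per three-month period. A later study of remote monitoring will need to know what the device contributes once a weekly questionnaire is in place. The planned contrast holds the device fixed and varies the questionnaire, so it cannot supply that figure.

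A second gap is related. The objective on RA-FQ accuracy against clinical flare calls for the RA-FQ as the predictor or index test. The refit described has accelerometry as the predictor and RA-FQ flare as the outcome, so it does not clearly deliver the objective.

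**Working it through.** **Role of each stream in each planned analysis**

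| Analysis | Longitudinal input | Outcome modelled | Scored against |
|---|---|---|---|
| Primary landmark model | accelerometry | clinical flare | clinical flare; also RA-FQ flare item |
| Secondary refit | accelerometry | RA-FQ flare item | clinical flare |
| Combined model | accelerometry + RA-FQ total | clinical flare | compared with accelerometry-only |
| RA-FQ only | not described | – | – |

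Every model described contains accelerometry. The difference between the combined and RA-FQ-only models cannot be formed from these outputs.

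**How far the planned result leaves the device's increment open**

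The AUCs and correlations in this part are assumed; the protocol gives none for the separate streams. Take two binormal markers with equal variances, within-group correlation ρ and the optimal linear combination:

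- d = √2 · Φ⁻¹(AUC) for each marker
- D² = (d_A² + d_Q² − 2ρ·d_A·d_Q) / (1 − ρ²), and combined AUC = Φ(D/√2)
- Solving for the questionnaire: d_Q = ρ·d_A + √[(1 − ρ²)(D² − d_A²)]

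Fix the two quantities that the plan would report: accelerometry-only 0.70 (d_A = 0.742) and combined 0.82 (D = 1.295). The planned contrast is then 0.12 in every row below. D² − d_A² = 1.126.

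| ρ | d_Q | RA-FQ-only AUC | Device adds to RA-FQ |
|---|---|---|---|
| −0.2 | 0.891 | 0.736 | 0.084 |
| 0 | 1.061 | 0.773 | 0.047 |
| 0.3 | 1.235 | 0.809 | 0.011 |
| 0.5 | 1.290 | 0.819 | 0.001 |

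The same reported pair fits a device with a clear contribution and one with almost none.

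**Dependence on the assumed values**

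Taking the two single-stream AUCs as the inputs instead:

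| Device AUC | RA-FQ AUC | Device adds, ρ = 0 | ρ = 0.4 | ρ = 0.623 |
|---|---|---|---|---|
| 0.70 | 0.80 | 0.039 | 0.007 | 0.000 |
| 0.80 | 0.80 | 0.083 | 0.043 | 0.025 |
| 0.80 | 0.70 | 0.139 | 0.107 | 0.100 |

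A redundant device is one possibility among several. It is most plausible if the device is the weaker stream.

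**What 100 patients were sized for**

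Target Recruitment Sample Size tests one AUC: 0.8 against 0.6, 50% flares, two-sided 0.025, 90% power. With 50 flares and 50 non-flares, the Hanley-McNeil standard errors are 0.0566 at 0.6 and 0.0445 at 0.8. Power is Φ[(0.20 − 2.241 × 0.0566)/0.0445] = Φ(1.64) ≈ 95%. The required N is 85 with Hanley-McNeil variances, 90 with Obuchowski variances, and 98 with the Obuchowski null variance only. The target of 100 is therefore adequate for that test.

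**Precision of the missing contrast**

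I simulated 50 flares and 50 non-flares with device AUC 0.70, RA-FQ AUC 0.80, ρ = 0 and known optimal weights. The true increment is then 0.04. The SD of the difference between combined and RA-FQ-only AUC is 0.026. An approximate 95% interval is 0.04 ± 1.96 × 0.026, or −0.01 to 0.09. Estimating the weights would widen it.

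**The case against.** The case for leaving the plan alone has four parts.

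- **The analysis matches its question.** The Abstract, Textbox 1 and Secondary Analyses all ask whether the RA-FQ adds to accelerometry. The planned contrast answers that and credits the gain to the RA-FQ. This stands: the contrast is not an error, and the protocol nowhere offers it as evidence for the device.
- **A comparison of the two streams is intended.** An objective covers RA-FQ accuracy against clinical flare, and Principal Findings speaks of comparing model-based prediction with RA-FQ flare detection. This stands in part. Sensitivity and specificity for the questionnaire would be useful, but they are not a model on the same landmarks and horizon and cannot be subtracted from the combined model's discrimination or calibration. The analysis described does not clearly produce them either.
- **A further comparator could sit in an unseen analysis plan.** It could. But the article states the comparison more than once, always in one direction, and gives its purpose.
- **The new contrast will be imprecise.** It will, as the simulation shows. That argues for reporting it as an estimate, not for omitting it.

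A reader might infer that the study can never tell whether the wearable adds anything. The documents do not support that: the RA-FQ is completed weekly ("The questionnaire will be collected weekly for each patient"), so the data will exist and only the analysis is absent. A reader might also infer that a gain over accelerometry alone is equally compatible with a useful and a redundant device. That depends on assumed AUCs. Nor does Strength and Limitations contradict Secondary Analyses: the sentence is hedged and also counts clinician assessment as part of the multimodal design.

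**Conclusion.** The concern holds as a gap in the planned comparisons, not as a mistake in the one stated. The plan estimates the RA-FQ's increment over accelerometry and leaves the reverse increment unestimated. Without it, the results would not support saying that the multimodal approach improves on each single stream, or that the device adds to a weekly questionnaire.

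That conclusion rests on the protocol text alone. The range of 0.001 to 0.084 AUC rests on assumed binormal markers and assumed AUCs of 0.70 and 0.82; it shows only that the planned result does not fix the device's increment. The point is worth acting on because the change is cheap and can still be prespecified: 16 participants had been recruited by July 1, 2026, and the main analysis waits for completed follow-up.

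**What to change.** In Secondary Analyses, add a landmark model for clinically confirmed flare with the RA-FQ total score as its only longitudinal predictor. Use the same patients, weekly landmarks, 14-day horizon, baseline covariates and validation as the other two models. Report combined minus RA-FQ-only beside combined minus accelerometry-only, for discrimination and calibration. Give patient-level bootstrap intervals, since each patient contributes many landmarks.

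Label both differences as exploratory estimates, because the sample size was set for a single AUC against 0.6 and not for an increment. Base any statement about the wearable's added value over the RA-FQ on the first difference. The same model would also give the objective on RA-FQ accuracy against clinically confirmed flare an analysis in which the RA-FQ is the predictor.

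The cost is one extra model on data already being collected, with no change to study procedures. The downside is a probably wide interval, which the report should state plainly.

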### Missing Data

If any accelerometry-driven data are missing for a patient, the last observation carried forward (LOCF) method will be applied, as these data are collected daily and LOCF reflects the information available at the time of prediction. For the RA-FQ, if any item is missing for a patient, it will be replaced using the LOCF method, as the questionnaire is collected weekly.

For quantitative feedback from the participant acceptability questionnaire, missing responses in Section A will not be imputed, as they reflect participants’ perceptions at the time of data collection. For the overall satisfaction score (0‐100), missing values will also not be imputed, and analyses will be based on observed data only.

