### Data Analysis

#### Preprocessing of Accelerometry Data

Axivity AX6 device data will be processed using established, standardized pipelines to derive quality metrics and daily summary metrics from the raw 3-dimensional acceleration and gyroscope signals, covering activity outcomes including volume (eg, step count), pattern (eg, distribution of activity across the day), and variability [20,21]; mobility outcomes including pace and rhythm variability [22]; and sleep outcomes including duration and sleep bouts, defined as interruptions [23].

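### Last observation carried forward, as written for the RA-FQ, also fills in the yes/no current-flare answer, which is a reference standard and a model outcome rather than a predictor

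*Protocol article*

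**What the plan says.** All places are in the protocol article.

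- **Missing Data** gives one rule for the questionnaire: "For the RA-FQ, if any item is missing for a patient, it will be replaced using the LOCF method". The weekly schedule is the only reason offered.
- **RA-FQ** (under Descriptive Analyses) puts the flare question inside the instrument. Two yes/no questions follow the 0–10 ratings, and the second asks patients "whether they believe they are currently experiencing a flare of RA".
- **Primary Analyses** derives patient-reported flare "based on responses to the yes or no question about current flare status" and adds: "Patient-reported flare status will serve as the reference standard". Sensitivity, specificity and Cohen κ are computed against it. Textbox 1 lists this comparison among the primary subobjectives.
- **Secondary Analyses** refits the landmarking models with patient-reported flare from the RA-FQ as the outcome.
- **Missing Data** has two neighbouring rules. For accelerometry, carry-forward is justified because it uses what is known when the prediction is made. Acceptability answers in Section A are left missing, because they express what the participant felt when asked.

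**The concern.** One rule serves two kinds of variable. An RA-FQ score available at a landmark is a predictor, and using its last known value mimics what a clinic would have in hand. The current-flare answer, as used in Primary Analyses and in the refit, is the truth against which a prediction is judged, and it is observed after the landmark. The accelerometry justification does not extend to it. The reason the same section gives for not imputing acceptability answers fits it well, since 'are you in a flare now' is also a perception at one moment.

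Carried forward, the label goes wrong in two ways. If the last answer was 'no' and a flare starts in an unanswered week, that week is labelled 'no'. If the last answer was 'yes' and the flare resolves in an unanswered week, that week is labelled 'yes'. The accuracy figures for a primary subobjective would then rest partly on copied labels, and onset in the refitted time-to-event models would be late or lost for some participants.

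**Working it through.** **What is fixed by the text.** The article states no figure for this point, so there is none to reproduce. The chain is textual: the rule covers any item; the flare question is an item of the RA-FQ; the answer to that item is the reference standard and the refit outcome. No sentence exempts it.

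**Inputs for size.**
- From the article: weekly collection, a 14-day prediction horizon, a flare risk of about 50%, and 52 weeks (the longest follow-up described).
- Assumed, not in the article: a share *m* of weeks unanswered at random (20% or 30%); one flare lasting *D* weeks (2 or 4) in half the patients; true weekly sensitivity 0.80 and specificity 0.90; first week answered.

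**Step 1, false 'no' weeks.** Week *j* of a flare is labelled 'no' only if weeks 1 to *j* are all unanswered, probability m^j. The expected number per flare is S = m + m² + … + m^D.

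**Step 2, false 'yes' weeks.** Week *k* after a flare is labelled 'yes' only if the flare was recorded (probability 1 − m^D) and post-flare weeks 1 to *k* are all unanswered. The expected number is (1 − m^D) × m/(1 − m), which also equals S. So 'yes' labels still average *D* per flare, but *S* of them are wrong.

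**Step 3, measured accuracy.** The alarm rate is 0.80 in a true flare week and 0.10 otherwise. Two patients give 104 weeks and one flare.
- Sensitivity = 0.80 − 0.70 × S/D
- Specificity = 0.90 − 0.70 × S/(104 − D)

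| m | D | S | Unanswered flare weeks labelled 'no', S/(D·m) | Flare never recorded, m^D | Sensitivity | Specificity |
|---|---|---|---|---|---|---|
| 20% | 4 | 0.2496 | 31% | 0.2% | 0.756 | 0.898 |
| 20% | 2 | 0.2400 | 60% | 4% | 0.716 | 0.898 |
| 30% | 4 | 0.4251 | 35% | 0.8% | 0.726 | 0.897 |
| 30% | 2 | 0.3900 | 65% | 9% | 0.664 | 0.897 |

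A simulation of the same set-up (20,000 patients per scenario) gave sensitivities of 0.760, 0.721, 0.724 and 0.665 in the same order. Scoring answered weeks only gave about 0.80 and 0.90 throughout.

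**Step 4, non-response related to flare.** Take 50% unanswered in flare weeks, 30% otherwise, D = 2.
- False 'no' weeks: 0.5 + 0.25 = 0.75, so 0.75/(2 × 0.5) = 75% of unanswered flare weeks.
- Flares never recorded: 0.5² = 25%.
- False 'yes' weeks: 0.75 × 0.3/0.7 = 0.321.
- Sensitivity: (0.80 × 1.25 + 0.10 × 0.321)/(1.25 + 0.321) = 0.657 (simulation 0.653).

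**Step 5, 14-day windows.** Suppose a rolling two-week window counts as flare if either weekly answer is 'yes', with 0.80 and 0.90 now applying per window. A flare covers D + 1 windows. False 'no' windows are S + m^D (an unrecorded flare loses all D + 1), and false 'yes' windows are S. Sensitivity = [0.80 × (D + 1 − S − m^D) + 0.10 × S]/(D + 1 − m^D).
- m = 20%, D = 4: (0.80 × 4.7488 + 0.02496)/4.9984 = 0.765
- m = 30%, D = 2: (0.80 × 2.52 + 0.039)/2.91 = 0.706

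**The case against.** **The rule may be narrower than it reads.** It is worded by item, and the article does not say what happens when a whole weekly questionnaire is absent. The RA-FQ section also calls the ratings scale items and the flare entries questions. An analysis plan not shown might exempt the flare question. This lowers certainty about how many labels would be copied. It does not remove the point: 'any item' makes no exception, and a single skipped flare question would still be copied.

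**A copied label is not necessarily a wrong one.** This stands. With 20% of weeks unanswered, 20% of labels are copies, but most fall in quiet periods and are correct. A reader might infer that every unanswered week yields a false label; the article does not support that. The error sits around onset and resolution.

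**A 14-day window holds about two questionnaires.** A missed onset week need not mislabel a window if the next answer is 'yes'. This stands in part. The window that ends in the onset week is still mislabelled, and Step 5 shows the loss reduced, not removed (0.706 instead of 0.664 in the least favourable random case).

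**Dropping unanswered weeks does not cure informative non-response.** Correct. In the simulation with 20% missing outside flares and 40% within 4-week flares, true κ was 0.333, answered weeks alone gave 0.278, and carry-forward gave 0.283. The fix therefore needs a sensitivity analysis as well.

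**A reader might extend the point to accelerometry,** where "If any accelerometry-driven data are missing for a patient, the last observation carried forward (LOCF) method will be applied", and argue that copied days shrink the variability features. The article does not support this. It lists "pattern (eg, distribution of activity across the day), and variability" among metrics derived from the raw signal as daily summaries, defines no window over which day-to-day variance is taken, and gives a real-time reason for carrying a predictor forward. Limits on carry-forward and wear-time rules may properly be left to the analysis plan.

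**Conclusion.** The point holds in a limited form. As written, the RA-FQ rule imputes a reference standard and a model outcome by copying an earlier answer, for a reason that suits neither use. It touches the patient-reported flare comparison (a primary subobjective) and the patient-reported-outcome refit (secondary).

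A reader might infer that the main model is compromised. It is not: the clinically confirmed flare outcome and the AUC behind the sample size do not use this label. Carrying RA-FQ symptom scores forward as landmark predictors in the combined model is also defensible.

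The effect falls mainly on sensitivity. Under the assumptions shown, weekly sensitivity of 0.80 reads as roughly 0.76 to 0.66, or about 0.77 to 0.71 on two-week windows, and weekly specificity stays within 0.003 of 0.90. These figures depend on missingness and flare duration, neither of which the article gives, so they illustrate the mechanism and do not forecast this study. The correction should be made before analysis. With 16 of 100 participants recruited by July 1, 2026 and outcome analyses still to come, there is time.

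**What to change.** In Missing Data, split the RA-FQ rule by use:

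1. Apply carry-forward only to RA-FQ symptom items or the total score when they enter a model as landmark predictors.
2. Leave the current-flare answer missing when it is unanswered, whether one question or the whole questionnaire is absent.
3. For sensitivity, specificity and κ, score prediction windows on observed answers only.
4. In the refit with patient-reported flare as outcome, follow each person to the last answered week, and treat an onset first seen after a gap as lying between the last 'no' and the first 'yes'.
5. Report weekly RA-FQ completion, and add a sensitivity analysis in which non-response is related to flare.

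The cost is a change of wording and one extra analysis. Some weeks or windows will drop out of the accuracy tables, so those estimates will be somewhat less precise. Data collection does not change.
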